**Discussion:**

This randomised controlled trial (RCT) will evaluate the efficacy of a nature-based intervention in reducing PTSD symptoms in military veterans and frontline workers such as emergency service personnel and contribute to the evidence base on the clinical impact of NBIs for mental health outcomes.

**Trial registration:**

ISRCTN13593648. Registered on 19 June 2024

## Administrative information

Note: The numbers in curly brackets in this protocol refer to SPIRIT checklist item numbers. The order of the items has been modified to group similar items (see http://www.equator-network.org/reporting-guidelines/spirit-2013-statement-defining-standard-protocol-items-for-clinical-trials/).

## Introduction

### Background and rationale {6a}

This project addresses the critical issue of post-traumatic stress disorder (PTSD) in military veterans and emergency service personnel. PTSD, characterised by trauma-induced symptoms, often results in impaired functioning and comorbid conditions such as depression and anxiety [1, 2]. Existing psychotherapeutic treatments are associated with significant barriers for veterans and others, including delayed help-seeking, lengthy waiting times, and a lack of military-specific knowledge among healthcare professionals [3]. In response to these challenges, this study proposes a nature-based angling intervention as a novel approach, leveraging the potential benefits of nature-based interventions (NBIs) for mental health.

The need for innovative treatments is underscored by the limitations and reduced effectiveness of current therapies for veterans [4, 5]. The proposed angling intervention, developed over 7 years, aims to provide a local, cost-efficient, and accessible solution. Previous trials indicated significant improvements in PTSD, anxiety, and depression following a single 2-day intervention, with peer-supported angling proving particularly effective [6]. This study’s inclusion of emergency service personnel acknowledges their elevated risk of PTSD and seeks to provide much-needed evidence for NBIs in this understudied population.

The choice of angling as the intervention is justified by its broad appeal, accessibility, and potential for year-round engagement. The intervention’s delivery is facilitated by a not-for-profit community interest company (iCARP CIC), emphasising collaboration with military veterans and aligning with broader initiatives that promote angling for well-being. The research commissioned by the NIHR-PRP aims to contribute robust experimental evidence of the causal impact of NBIs to support the integration of NBIs into mental health care policy, potentially reducing the social and economic costs of untreated PTSD within the community.

We aim to conduct a fully powered randomised waitlist-controlled trial of an angling based NBI for people with PTSD. This study builds upon a developmental phase of the project, where the feasibility of the intervention and all measures were rigorously tested and validated. It represents a significant step towards addressing the mental health needs of veterans and emergency service personnel, offering a promising alternative to conventional treatments. The outcomes may not only improve the well-being of these populations but also inform broader mental health policies, emphasising the role of nature-based interventions in promoting mental health and resilience.

### Objectives {7}

Primary outcome objectivesAssess mean changes in mental health outcome measures (e.g. PTSD, see item “Outcomes {12}” for a full list) from pre- to post-intervention between active and control groups (see item “Statistical methods for primary and secondary outcomes {20a}” for analysis details).Secondary outcome objectivesAssess proportion of participants achieving clinically significant change and reliable change between 2-week pre- and 4-week post-intervention PTSD scores.Conduct sub-group analyses to evaluate mean change in primary outcomes by stratification factors (military veteran vs. ESP, PTSD severity, gender).Assess mean change in social loneliness, work and social adjustment, and anger expression from pre- to post-intervention between active and control groups.Assess mean change in primary outcome measures from baseline to 6 months and 12 months for the active intervention group only.Assess mean change in process measures (e.g. mood, see item “Outcomes {12}” for a full list) and physiological data (heart rate variability and eye movement) from day 1 to day 2 of the NBI experience.Assess the relationship between intervention experiences and changes in process measures from day 1 to day 2 of the intervention and their relationship to change in outcomes.We will also explore the cost-effectiveness and social return of investment of the intervention.

### Trial design {8}

A randomised waitlist-controlled superiority trial with an allocation ratio of 1:1 and a 4-week follow-up. The primary outcome will be assessed at 2-week and 4-week post-intervention and compared with the waitlist control group. The total follow-up period is 12 months (intervention group only).

## Methods: participants, interventions, and outcomes

### Study setting {9}

The intervention will be run by iCARP CIC at their “Lifted Lakes”, a single mental health and wellbeing centre in Great Oakley, Essex, UK.

### Eligibility criteria {10}

This includes UK armed forces veterans or emergency service personnel (current or former). Therefore, those not a military veteran or member of the emergency services (current or former) will be ineligible. Angling coaches, delivering the intervention, require an Angling Trust Level 2 Coaching Certificate.

### Who will take informed consent? {26a}

The registration form, delivered via an online platform (Qualtrics), provides further information for participants and a mechanism for providing informed consent.

### Additional consent provisions for collection and use of participant data and biological specimens {26b}

The consent form asks if participants would be happy to be contacted in the future about research participation. Participants can say no to this and still part in the study.

## Interventions

### Explanation for the choice of comparators {6b}

A randomised, waitlist control group will be used as the comparator. With an intervention such as this, it is not possible to employ a well-balanced placebo condition, and a waitlist control is therefore commonly used in psychological studies. It is also an ethical alternative to a no-treatment option, as all participants receive the intervention eventually.

### Intervention description {11a}

The intervention is named *Casting Away Trauma* (CAT). Following our preliminary work and the developmental phase of the current project, we have a well-established and manualised protocol for the intervention:Day 1 am — Arrival at fishing lake, introduced to personal angling coach, shown to designated lakeside “swim” with tent and seat, health and safety briefing, set-up equipment, and recording of “arrival” process measuresDay 1 pm — Fishing instruction, fishing and social interaction, evening meal, and participants fish through the night or sleep as they chooseDay 2 am — Breakfast, fishing, and social interactionDay 2 pm — Fishing and pack-up equipment, recording of “departure” process measures, instructions on how to keep in contact via social media, etc.

Prior to their intervention, participants will be sent a letter and an infographic developed for the study visualising what to expect at the intervention. The venue will be available exclusively to participants. Professional angling coaches with Angling Trust certification will be provided at a ratio of 1:2 participants. As recommended by Husk et al. [7], participants will be supported to travel to the venue. iCARP’s “Lifted Lakes” venue has a covered socialising area with a fire pit, and participants are encouraged to bring warm clothing, since socialising with peers is a key component of the intervention. Participants are free to move around the lake and talk to other participants and use the communal area for socialising and taking warm drink breaks. Food will be cooked and shared by iCARP volunteers. At the end of the experience, participants will be encouraged to join a “Facebook” group in order to keep in contact via social media and will be offered a selection of exit routes. During this period, the wait group receives no intervention and continue with their normal day-to-day activities and usually care.

### Criteria for discontinuing or modifying allocated interventions {11b}

Participants may drop out of the study without giving a reason. However, any data collected up to the point of withdrawal will be retained unless requested otherwise. Criteria for discontinuation during the 2-day intervention period is handled by a mental health specialist on a 1 to 1 basis. Should mental health first aid be required during the intervention, the participant will be given the option to discontinue or continue with the intervention, and a collaborative decision can be formed as to the future support required, and then referrals to appropriate external services can be made if required.

### Strategies to improve adherence to interventions {11c}

The intervention takes place over 2 days/1 night. Attendance logs are taken of active group participants arriving for the intervention. In the week prior to the intervention, participants are contacted by telephone and reminded how to find the venue. They are also given reassurance about what they will have to do during the 2-day intervention. Participants who attend the intervention are also compensated £50 GBP towards their travel expenses. Waitlist control group activities are not monitored.

### Relevant concomitant care permitted or prohibited during the trial {11d}

Usual care for participants continues throughout the trial. There is nothing prohibited.

### Provisions for posttrial care {30}

As this trial consists of one (per participants) nondrug intervention that lasts 2 days/1 night, there is minimal risk other than risks associated with being near water. In case of psychological distress (e.g. “flashbacks”), a mental health professional will be present at all interventions in order to observe and monitor for any signs of distress. The mental health professional’s role will be to administer mental health “first aid” to any participants whose PTSD symptoms might be triggered during the day. First aid will include grounding techniques, emotional regulation procedures, and psycho education around the symptoms they may be experiencing. Signposting will also be given, where access to additional care can be sought. In the week prior to the intervention itself, the mental health professional contacts participants attending to help alleviate any apprehension participants might be feeling about attending the intervention.

Following consultation with various mental health and wellbeing service care providers, we appreciate the importance of having a targeted and varied exit strategy for participants leaving the study. Consequently, we have devised an array of options for our participants allowing a choice of levels of engagement:Do not wish to fish again.Wish to fish again independentlyWish to fish again with advice from iCARP CICWish to fish again with iCARP CICWish to volunteer to help iCARP CICWish to train to be an iCARP CIC angling coach

Participants will indicate which of these five options they prefer at the 4-week follow-up. At the end of the 2-day intervention, participants will be given a “Keep in Touch” information sheet that will include these options and an invitation to 

#### Compensation for harm

The University of Essex provides indemnity against negligent harm caused as a direct result of an employee’s or a student’s actions. The chief investigator is an employee of the University of Essex.

### Outcomes {12}

#### Primary outcome measures

The following measures will be employed to evaluate the effectiveness of the intervention and will be assessed 2 weeks before the intervention and 2-week and 4-week post-intervention. The National Institute for Health and Care Excellence (NICE) [8], recommends the use of self-report measures for evaluation of outcome in PTSD interventions. These measures of PTSD, anxiety, depression, and wellbeing were used in the development phase, establishing their acceptability and sensitivity to change over the short to medium term: PTSD symptoms are assessed by the PTSD Checklist for DSM-5 (PCL-5) [9], Depression by the Patient Health Questionnaire-9 (PHQ-9) [10], and Anxiety by the General Anxiety Disorder-7 Scale (GAD-7) [11]. Participants will also complete the 7-item Short Warwick-Edinburgh Mental Wellbeing Scale (WEMWBS) [12] to evaluate positive feelings of wellbeing. Mean change from baseline will be assessed for each of these outcomes for active intervention and control groups.

#### Secondary outcome measures

Use subheadings (or just numbers that correspond to the objectives) under this heading following the same order as in the introduction statement of objectives:Using scores on the PCL-5 [9], we will assess the proportion of participants achieving clinically significant change and reliable change between 2-week pre- and 4-week post-intervention in the following ways: clinically significant change equates to a decrease in PTSD score of greater than or equal to 10, and reliable change reflects a decrease in PTSD score of greater than or equal to 5.Sub-group analyses will be carried out to evaluate mean change in the primary outcome measures (described above) by stratification factors (military veterans vs emergency service personnel), PTSD severity (high vs low), and gender (male vs female).The following measures of loneliness and expressed anger were included in the developmental phase and will be assessed as follows: Loneliness will be assessed by the Short Version of the Social and Emotional Loneliness Scale for Adults (SELSA-S) [13]: 2 weeks prior and 2- and 4-week post-intervention. Expressed anger will be assessed by the State–Trait Anger Expression Inventory (STAXI) [14], which measures how frequently participants have expressed anger verbally or physically in the last month. This will be taken 2-week pre-intervention and 4-week post-intervention. The Work and Social Adjustment Scale (WSAS) [15] is a 5-item measure of impairment in general social functioning. This will be measured 2-week pre-intervention and at a 6-month and 12-month follow-up since it will not be sensitive to short-term change. Mean change from baseline will be assessed for each of these outcomes for active intervention and control groups.Follow-up measures at 6 and 12 months: It is not possible to include long-term follow-up measures in the RCT because the waitlist group will receive the intervention after the RCT 4-week data collection is completed. Instead, we will take measures of PTSD symptoms, anxiety, depression, wellbeing, loneliness, expressed anger, and social functioning, to provide pre- and post-data from the intervention fishing group only at 6 months and 12 months after their intervention. We will also measure changes in NHS (National Health Service) service use and employment at these times. In addition, to gauge the impact of the NBI on long-term behaviour and engagement with nature-based activities, we will follow-up on the participant exit strategy to assess how participants have engaged with angling or other nature-based activities since the intervention. Mean change from baseline to follow-up will be assessed.Mean changes in process measures (mood and physiological changes) will be assessed between the beginning of day 1 of the intervention to the end of day 2. We will evaluate mood using the brief Profile of Mood States (POMS) [16]. Our developmental phase has shown that these measures are sensitive to detect change between arrival and departure at the intervention. Following consultation in the development phase, we include objective physiological measures of psychological states: pulse heart rate and heart rate variability and assess hypervigilance using a mobile eye-tracking device to quantify saccadic behaviour.*Measures of the hypothesised active elements of the intervention*: We developed an item pool during the developmental phase. These measures will be taken prior to departure. Eight items from the Perceived Restorativeness Scale (PRS) [17] measure perceived experience of restoration from the environmental surroundings. Bespoke questions have been developed to evaluate self-efficacy, experience of fishing, and being in a group of veterans. Fourteen questions explore participants’ experience of fishing (e.g. “I found I could focus on the fishing”). Eleven questions explored participants’ experience of peer support over the weekend (e.g. “I felt the people around me understood”). These questions are answered by participants at the end of day 2 of the intervention. We will assess the relationship between intervention experiences and changes in process measures and any potential interaction with outcome measures over the course of the trial.The cost-effectiveness and social return of investment will be analysed based on the Greater Manchester Cost-Benefit Analysis Model [18]. This will allow for comparisons to be made with other treatments and studies using government-approved values.

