## Assignment of interventions: allocation

### Sequence generation {16a}

Participants will be allocated to the control or waitlist condition by covariate adaptive randomisation, a valid technique for clinical trials [19, 20] where specific participant characteristics (covariates) can be controlled for on a sequential basis based on recruitment and allocation to date [21, 22]. Randomisation will be implemented using Sealed Envelope (https://www.sealedenvelope.com), an online randomisation service. It applies a minimisation algorithm with a random component. The minimisation algorithm will balance groups on the following pre-specified covariates: gender, PTSD symptom severity (PCL-5 score) [9], and service group (military veterans vs nonmilitary service personnel vs a mix of both). PTSD symptom severity will be dichotomised into low and high categories using a fixed median split based on baseline PCL-5 scores from the initial cohort of participants enrolled prior to commencement of full randomisation (*N* = 48). This median cutoff-point will be calculated once and applied consistently to all subsequently enrolled participants and will not be updated during recruitment. For each new participant, the algorithm will calculate the marginal imbalance that would result from assignment to each group across the stratification variables. Participants will be assigned to the group that minimises overall imbalance, with a probabilistic random element (e.g. 80% allocation to the group minimising imbalance) to maintain allocation concealment and reduce predictability. The randomisation schedule will be devised prior to recruitment using an online tool and applied to eligible participants recruited online after participant identification numbers have been assigned.

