#### Secondary analyses

We will assess if the changes in PTSD symptoms observed might be considered clinically significant or reliable. We will assess clinically significant change (a decrease of > = 10 points on the PCL-5) and reliable change (as decrease of > = 5 points on the PCL-5) between the baseline and 2-week and 4-week post-intervention. All analyses will be carried out on veterans and emergency service personnel combined.Subgroup analysis of primary outcomes by stratification factors will be conducted using mixed MANOVA (intervention vs waitlist) × repeated measures on all outcomes (baseline vs 4-week post-intervention) separately for each stratification factor.A mixed MANOVA with one between-group factor (intervention vs waitlist control) and repeated measures on secondary outcomes (loneliness, expressed anger, work and social adjustment)Within-participant analyses will be used to assess change from baseline to 6 months and 12 months for the intervention group only.A psychometric analysis of process measures will be conducted via factor analysis and reliability analysis. Path analyses will explore the relationship of process measures regarding the intervention experience to mood change assessed via the POMS questionnaire and psychophysiological data during the intervention and change in outcomes.See item e. above.A cost-benefit analysis will be used to analyse the cost of effectiveness and social return of investment of intervention based on the Greater Manchester Cost-Benefit Analysis model, which allows for comparisons with other treatment/projects based on government-approved values.

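### Effect modification by PTSD severity is analysed only as high versus low, although the continuous pre-randomisation PCL-5 is available: a cheap improvement to a secondary analysis

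*Protocol article*

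**What the plan says.** The Objectives section (item 7) makes subgroup analysis of the primary outcomes by stratification factor a secondary objective. PTSD severity is one of three such factors. Secondary outcome measures (item 12) fixes the form: "PTSD severity (high vs low), and gender (male vs female".

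Secondary analyses (item 20a) gives the method: "Subgroup analysis of primary outcomes by stratification factors will be conducted using mixed MANOVA (intervention vs waitlist"), run "separately for each stratification factor". It names no cut-off for severity, no continuous-severity model and no explicit treatment-by-severity test.

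High and low are defined only in Sequence generation (item 16a), for minimisation. Severity is "dichotomised into low and high categories using a fixed median split based on baseline PCL-5 scores from the initial cohort of participants", namely those "enrolled prior to commencement of full randomisation (*N* = 48"). The cut-off is then frozen: "This median cutoff-point will be calculated once and applied consistently to all subsequently enrolled participants and will not be updated during recruitment".

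Recruitment (item 15) says that PCL-5 items are part of the registration form and are used for randomisation, so a numerical score exists for everyone before allocation.

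**The concern.** Two categories are a sensible input to a minimisation algorithm, and that use is not at issue. Allocation does not require the analysis to use the same categories.

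On a split scale, participants just either side of the cut count as different, while the mildest participant and one just below the median count as the same. A gradual change of effect with severity is then harder to detect. A high-versus-low result is also hard to apply elsewhere. If the cut is the one used for minimisation, it is the median of a small early sample, and the protocol cites no clinical threshold for it.

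This matters because the Discussion says the findings should inform policy and the commissioning of social prescribing, where a natural question is who benefits at what severity. The sample size was set for the main comparison only, so the severity question starts with limited information.

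**Working it through.** **Plan's own figure.** Sample size (item 14) gives d = -0.52, two-sided alpha 0.05, power 95% and 98 per arm. A two-sample t calculation needs 97.09 per arm, so 98 per arm or 196 in total, with 95.2% power. The figure reproduces. It concerns the main comparison; no power is stated for any subgroup analysis.

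**Assumptions not in the protocol.** Severity X is standard normal, the treatment effect changes linearly with X by beta SD per SD of severity, the residual SD is 1, and 196 participants are analysed, 98 per arm.

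**Information kept by a split.** For a cut at c with proportion p below it, relative efficiency is phi(c)² / [p(1 - p)], where phi is the standard normal density.
- At the median this is 0.3989² / 0.25 = 2/pi = 0.637, so 36.3% is lost.
- Direct check: the continuous interaction has standard error 2/√196 = 0.143. The split contrast is 2 × 0.798 × beta with standard error 4/√196 = 0.286. The ratio of non-centralities is 0.798, and 0.798² = 0.637.

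**Power, two-sided alpha 0.05.** The non-centrality is multiplied by 0.798.
- 80% power: 2.80 × 0.798 = 2.23, giving 60.9%, a loss of 19.1 points.
- 90% power falls to 73.4%, a loss of 16.6 points.
- The largest loss at any non-centrality is 19.4 points (75.5% to 56.1%). This maximum does not depend on the sample size.

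**Cut-off estimated from 48 people.** The sample median has a standard deviation of about 0.18 SD, so the proportion below the cut has a 95% range of about 36% to 64%. Mean efficiency is 0.629 (37% lost), with a largest loss of 19.8 points. At the unfavourable end of that range efficiency is 0.60 and the largest loss is 21 to 22 points.

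**Simulation.** 196 analysed, cut from an independent 48, no severity main effect, 6,000 replicates:

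| Gradient (assumed) | Continuous | Split | Loss |
|---|---|---|---|
| 0.3 | 53% | 37% | 16 |
| 0.4 | 79% | 60% | 19 |
| 0.5 | 93% | 77% | 16 |

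A separate run at gradient 0.2 gave 28% against 19%, a loss of 9 points.

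**Sensitivity to the distribution of scores (exact median split).**
- Normal, mean 48 and SD 15 (assumed), truncated to 0–80: largest loss 18 points; truncated to 31–80: 16 points.
- Uniform: 12 points.
- Heavier tails than normal (t with 5 degrees of freedom): 26 points, though such tails are less plausible for a bounded questionnaire score.

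**Where the split does better.** If the true effect is a step exactly at the median, one simulated case gave 42% power for the continuous model and 48% for the split.

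**The case against.** Subgrouping by the factors used in allocation is conventional, pre-specified and easy to report. Fixing the cut-off early and never updating it prevents a cut being chosen from the results. The analysis is one of three subgroup factors within a secondary objective. All of this stands, and it is why the point is a minor improvement. None of it is a reason to leave the numerical score unused.

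It is also fair to say that the power figures do not describe a planned test. Item 20a plans a mixed MANOVA on several outcomes and names no interaction test. The figures above are for a single-outcome treatment-by-severity test, so they measure what the split costs the question, not a shortfall in a stated calculation.

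A reader might take it as stated that the median of the 48 is the analysis cut-off. It is not: item 16a gives it for minimisation, and items 12 and 20a give no cut-off. Nor do the subgroup levels simply copy the allocation levels, since service group has three categories in item 16a and two in items 7 and 12. Reuse is a strong inference from the reference to stratification factors. If a different cut were used, the remark about the early sample would fall away, but the analysis would still be binary.

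Nor is this a detail left to the later analysis plan that item 20c promises. The exact cut-off could be left to it, but the binary form is already fixed in item 12.

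**Conclusion.** The point stands as a cheap improvement to a secondary analysis. The protocol commits to a high/low comparison where a more informative analysis of data already collected is available. Under normality and a linear gradient, about 36% of the information on effect modification is lost, and at most about 19 to 20 points of power, the upper figure allowing on average for a cut taken from 48 people. For a bounded or truncated score the maximum is nearer 16 to 18 points, and it is lower again if the true gradient is weak.

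A reader might infer a larger cost, up to about 24 points. That does not follow from the split alone. In simulation at a gradient of 0.4, about 23 to 24 points appears only with treatment coded 0/1 and an assumed severity main effect of 0.3 left unmodelled within each half. With baseline severity as a covariate in the split model, or with no such main effect, the loss returns to about 20. The protocol supplies no basis for the extra assumptions.

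The primary analysis, the sample size and the use of two categories in minimisation are untouched.

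**What to change.** Keep the high/low category for minimisation, and keep a high/low table as a descriptive display. In Secondary outcome measures (item 12) and Secondary analyses (item 20a), define the severity analysis as treatment by continuous pre-randomisation PCL-5 score. Report the estimated treatment effect with its 95% confidence interval at stated PCL-5 values, for example the 25th, 50th and 75th percentiles, and check linearity with a quadratic or spline term. State which cut-off the descriptive table uses.

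The cost is a change of wording, with no new data and no extra participants. It can still be made before analysis: Trial status gives September 2026 as the end of recruitment, and item 20c has the detailed analysis plan agreed before data entry ends. The downside is a linearity assumption, which the data can check, and a slight loss of power if the true effect is a step at the median.
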